##### Parasite genotyping studies

Filter paper blood spots will be collected on #1 Whatman Filter Paper and stored individually in zip-lock plastic bags with desiccant. Dried blood blots will be cut into small pieces, placed in 1.5 ml micro centrifuge tube and lysed in 1 ml of sterile water for 10 minutes at room temperature. During this step, the tubes will be vortexed every 1-2 minutes. The tubes will then be centrifuged at 15,000 rpm for 5 minutes. After pouring off the supernatant, DNA precipitate will be resuspended in 10 volume of 5% chelex-100 (Biorad Laboratories Inc. Hercules, CA), and incubated for 20 minutes at 56oC with a brief vortex at high speed before and after incubation. The tubes will be placed in 100oC heating block for 8 minutes and vortexed briefly at high speed after incubation. After a final centrifugation at 15,000 rpm for 2 minutes to precipitate chelex-bound organic material, DNA-containing supernatants will be removed by pipette for PCR amplification. Yields from blood spots of about 2 cm diameters may be expected to be in the range of 50 to 100 ng total DNA. If alternative or automated extraction methods become available during the course of the study, they may be used.

Analysis of amplification of the Pfmdr gene will be conducted as follows(7,15). Multiplex PCR will be used to amplify products from both the pfmdr1 and β-tubulin genes in a single tube. PCR will be performed in a total volume of 25 µl containing PCR buffer, 3.0 mM MgCl2, 300 µM of each deoxynucleoside triphosphate, and Taq DNA polymerase, 300 nM each Pfmdr1 primer, 100 nM of each -tubulin primer, 150 nM of Pfmdr probe labeled with 5’ Fam and 3’ Tamra and 100 nM of -tubulin probe labeled with 5’ Vic and 3’ Tamra. Each assay will be performed in duplicate. Reactions will be carried out in a Rotorgene Real Time PCR system using the following cycling conditions: 1x 50oC for 2 min, 1x 95oC for 15 min and 50 cycles of 95oC for 15 sec and 60oC for 1 minute. Results will be were accepted as valid only if the copy number for control DNA samples are 0.8-1.2 for 3D7 and 2.8-3.2 for W2Mef , and if the difference between duplicate copy numbers is <50% of the average. The efficiency, E, will be calculated from the slope of a standard curve made from known dilutions of a reference DNA (E=10-1/slope). The copy number will then be calculated as: Copy# = EbtCtbt/EmdrCtmdr. Where Ebt and Emdr are the efficiencies for -tubulin and Pfmdr, respectively, and Ctbt and Ctmdr are the corresponding number of cycles to reach threshold.

SNPs within the Pfmdr gene will be detected using RT-PCR as follows(6,9). The four polymorphic sites in pfmdr1 to be analyzed are Asn86/Tyr86, Tyr184 /Phe184, Ser1034/Cys1034, and Asn1042/Asp1042. Briefly, fluorescent-labeled minor groove binding (MGB) probes have been designed specific to the polymorphic site for wild-type or mutant species. Following amplification, the genotype of the four polymorphic sites was determined by increase in fluorescent emission of the wild-type or mutant probes. The relevant primers and probes are shown in the following table:

| Pf MDR 1 Point mutation | Primer/Probe | Oligonucleotide Sequence (5’  3’) |
| --- | --- | --- |
| 86 | Forward | ATGTGCTGTATTATCAGGAGGAAC |
|  | Reverse | TTGTACTAAACCTATAGATACTAATGATAATATTATAGG |
|  | Asn (wt*) probe | 6FAM-ACCTAAAT**T**CATGTTCTTT-MGB-NFQ |
|  | Tyr (mut**) probe | VIC-ACCTAAAT**A**CATGTTCTTT-MGB-NFQ |
|  |  |  |
| 184 | Forward | AAGATGGACAATTTCATGATAATAATCCT |
|  | Reverse | AATACATAAAGTCAAACGTGCATTTTTTA |
|  | Tyr (wt) probe | 6FAM-CTTTTTAGGTTTAT**A**TATTTGGT-MGB-NFQ |
|  | Phe (mut) probe | VIC-CTTTTTAGGTTTAT**T**TATTTGGT-MGB-NFQ |
|  |  |  |
| 1034 | Forward | AAAAAGAAGAATTATTGTAAATGCAGCTT |
|  | Reverse | GGATCCAAACCAATAGGCAAAA |
|  | Ser (wt) probe | 6FAM-ATTC**A**GTCAAAGCGCT-MGB-NFQ |
|  | Cys (mut) probe | VIC-ATTC**T**GTCAAAGCGCT-MGB-NFQ |
|  |  |  |
| 1042 | Forward | AAAAAGAAGAATTATTGTAAATGCAGCTT |
|  | Reverse | TTTCCAGCATAACTACCAGTAAATATAAAAG |
|  | Asn (wt) probe | 6FAM-CAATTATTTATT**A**ATAGTTTTGC-MGB-NFQ |
|  | Asp (mut) probe | VIC-AATTATTTATT**G**ATAGTTTTGC |
|  |  |  |

Analysis of mutations in other genes associated with malaria drug resistance will be performed by RT-PCR, PCR-RFLP analysis or allele specific amplification(3,11). For example, the presence of the K76T mutation in the Pfcrt gene associated with chloroquine resistance will be detected by nested PCR amplification of a 145 bp fragment including the mutation site. Digestion with the restriction enzyme *Apo*I distinguishes between the sensitive and resistant alleles.

Multiplexed analysis of SNPs associated with drug resistance will be performed using Luminex technology as follows, in a modification of previously described techniques(1). The Luminex allele-specific primer extension product (ASPE) uses gene specific primers that are placed 5’ upstream of the variable base (SNP) in the amplified sequence with a variable 3’ end nucleotide that will be used to define the allele or SNP. These primers will be used to generate a fluorescently labeled allele-specific primer extension product (ASEP) using the PCR amplified gene product, DNA polymerase, SNP specific biotin labeled ddNTP and each of the other three non-labeled ddNTPs. The SNP specific primers contain a unique identifying sequence that is complimentary to a c-sequence covalently attached to fluorescent microspheres. Following reaction, the newly generated ASEP will be captured by the c-sequence labeled microsphere and analyzed by the Luminex 100 flow cytometer after development with streptavidin-phycoerythrin (SA-PE). Each microsphere will be assayed for its characteristic fluorescence and SA-PE. Only microspheres that contain both fluorescent tags will be considered a positive result. By knowing which biotin-labeled ddNTP was present in the well and c-sequence each microsphere possesses, the sequence of the variable 3’ end nucleotide can be determined.

### 2. Sample Size

The sample size is based entirely on the primary objective and primary hypotheses. Several approaches to calculating the sample size yield a sample size of ~100 subjects per group. For example, consider that we want to demonstrate that mefloquine-artesunate has an efficacy of less than 90%. If the observed efficacy is 80%, as observed in our recent trial in Kampot Province, then for a sample size of 100, the upper 95% confidence interval for the efficacy is 87%. Consider that we want to show that the efficacy of Malarone or piperaquine-DHA is greater than 90%. For a sample size of 100, if the observed efficacy of either regimen is ≥97.5%, as observed in a previous WHO study in Oddarmeanchey, then the lower 95% confidence interval will be at 91%. Similarly, in order to have a power of 90% to detect the difference between an efficacy of 95% in one regimen and 80% in another, a sample size of 100 is required.

### 3. Data Analysis

Data will be recorded on standardized case report forms, entered into an Access database, and exported for analysis in STATA, SPSS, and Mathematica.

Therapeutic Efficacy. Drug efficacy will be calculated as the percent of subjects not requiring alternative therapy during the 42-day course of the test and reported with 95% confidence intervals. This will be the primary analysis and, as recommended by WHO will be conducted as a per protocol (rather than intent to treat) analysis. One disadvantage of this approach is that data from subjects who drop out or are lost to follow up during the follow-up evaluation period are not used. As a secondary, alternative approach we will calculate the failure rate using Kaplan-Meier survival analysis. The failure rate will be calculated as 1-Π(ri-di)/ri , where ri is the number of subjects without a recrudescence just before time ti, di is the number who had a recrudescence at time ti, and Π is the product of the fractions, (r-d)/r, at all points, i. The drawback to this analysis is that it makes the assumption that the risk of recrudescence in the patients lost to follow-up is the same as that in those not lost. This may not be a good assumption. Therefore, sensitivity analyses will be performed to determine the effect on the reported failure rate of the extreme assumptions that either all patients lost to follow-up had recrudescences, or that they all did not have them.

Predictors of treatment failure. Data will be analyzed using standard statistical packages such as Stata, SAS or SPSS. Subjects will be categorized based on therapeutic outcomes, presence of the various genetic markers and other demographic and parasite factors that are putative determinants of treatment failure, e.g. age, parasite density, parasite clearance time. Bivariate associations will be examined between these markers and the outcomes. Chi square or Fisher’s exact tests for two-tailed significance at p <0.05 will be used for univariate frequency comparisons. Test for association at each marker will be performed, for example, one SNP at a time. Since this analysis is only powered to generate hypotheses, no correction will be made for multiple hypothesis testing. Variables significant in any of these analyses will be fit into a logistic regression model to identify factors that were collectively predictive of treatment failure.

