One adult tablet of Malarone contains 250 mg of atovaquone and 100 mg of proguanil hydrochloride. For adults weighing >40 kg the daily dose is 4 tablets; for subjects under 40 kg the dosage is as follows: 11‐20 kg, 1 tablet; 21‐30 kg, 2 tablets; 31‐40 kg, 3 tablets. The daily dose is given for three days, day 0, day 1, and day 2.

The doses for all medications will be given orally with water. Patients will remain in the clinic for observation for one hour after each dose. If they vomit within the hour, the dose will be repeated. If they vomit within an hour of the repeated dose, they will be withdrawn from the study and referred to a local clinician for possible parenteral malarial treatment.

*iv. Rescue therapy*

Treatment failures, defined as persistent or recurrent parasitemia during the 42-day follow-up, will be treated with oral quinine sulfate 10 mg salt/kg tid x 7 days plus tetracycline 1 gm. x 7 days.

*v. Adjunctive therapy*

Adjunctive therapy, including analgesics, anti-pyretics, or rehydration, will be given at the discretion of the health center medical staff, and is not considered part of the study treatment.

f. Source of Study Drugs

All study drugs will be provided by the Cambodian Ministry of Health, which procures them from WHO-recommended producers who follow current Good Manufacturing Practices.

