**g. Follow-up**

Subjects are asked to re-visit the study unit on days 1, 2, 3, 7, 14, 18, 21, 28, 35 and 42, plus any other day that he/she feels sick, in order to monitor clinical recovery/recurrence of malaria symptoms. In the event that a subject fails to re-visit the study unit on schedule, a member of the study team will visit the subject and encourage the subject to visit the clinic for the scheduled follow-up. Any adverse events associated with the treatment regimen will be recorded.

Any time a subject is referred to the physician for a reason other than routine follow-up, the physician-subject contact will be recorded.

The following conditions constitute cause for removing a study subject from the study:

1. An expressed desire by the subject to terminate participation

2. A determination by the on-site physician that the subject risks his/her health by further participation

3. Development of a serious disease, including severe malaria (WHO criteria, Appendix VII), that requires referral to hospitalized treatment

4. Development of an infection requiring antibiotic therapy

5. Inability to locate a subject on two consecutive scheduled visits

6. Ingestion of any anti-malarial by subject outside protocol parameters

The following prompts administration of rescue therapy:

1. Asexual parasitemia on day 2 > day 0

2. Asexual parasitemia fails to clear by day 4

3. Asexual parasitemia recurs on or between days 4 and 42.

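### The secondary Kaplan-Meier failure rate counts only recrudescences, so, read literally, rescued subjects who never cleared their parasites are not events

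*Protocol*

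**What the plan says.** Protocol B.1.e (iv, Rescue therapy) gives the definition: "Treatment failures, defined as persistent or recurrent parasitemia during the 42-day follow-up". Section g, Follow-up, lists three prompts for rescue: "Asexual parasitemia on day 2 > day 0", "Asexual parasitemia fails to clear by day 4" and "Asexual parasitemia recurs on or between days 4 and 42". A subject can meet the first two without ever having cleared.

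B.3, Data Analysis, sets the primary measure: "Drug efficacy will be calculated as the percent of subjects not requiring alternative therapy during the 42-day course of the test". It then offers a Kaplan-Meier failure rate as a secondary, alternative approach, computed as 1 − Π(ri − di)/ri, where "ri is the number of subjects without a recrudescence just before time ti" and "di is the number who had a recrudescence at time ti". The two extreme-case sensitivity analyses for subjects lost to follow-up are also worded in recrudescences.

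On the Day 42 page of the Appendix A case report form, ETF is an outcome code that remains available after PCR correction. Recrudescence appears there as a PCR result, set against reinfection.

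**The concern.** B.3 calls the Kaplan-Meier quantity a failure rate, but its event covers only part of what B.1.e calls failure. A subject rescued for persistent parasitemia is a failure in the primary proportion. In the formula as worded, that subject never enters di.

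The Kaplan-Meier analysis is there to answer the stated weakness of the per-protocol proportion, that data from drop-outs go unused. If the two analyses also treat non-clearance differently, a gap between them may come from the event definition and not from loss to follow-up, and the reader cannot tell which. Non-clearance is also of direct interest in a study prompted by possible artemisinin resistance.

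This is not a detail left for a later analysis plan: the protocol writes out the formula and defines both of its terms.

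**Working it through.** **Inputs.** From the sample-size section (B.2): 100 subjects per arm, and 80% observed efficacy for mefloquine-artesunate, hence 20 failures per 100. From B.3: the product-limit formula. From the primary hypothesis (A.2): the 0.9 threshold. Assumed, because the protocol gives no figure: k of the 20 failures never cleared, with k varied from 0; and complete follow-up.

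**The plan's own figure.** For 80/100 the protocol states an upper 95% limit of 87%. The exact (Clopper-Pearson) limit is 87.3%, Wilson 86.7%, Wald 87.8%. The stated figure reproduces with the exact or Wilson method.

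**Handling of the k subjects.** B.3 does not say what happens to a rescued subject who never cleared. With complete follow-up there are three possibilities:

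- Counted as events: failure rate = 20/100 = 20.0% for every k, equal to the crude rate.
- Left in ri as subjects without a recrudescence: failure rate = (20 − k)/100.
- Censored at rescue, before any recrudescence: failure rate = (20 − k)/(100 − k).

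| k of 20 never cleared | Counted as events | Left in ri | Censored at rescue |
| --- | --- | --- | --- |
| 0 | 20.0% | 20.0% | 20.0% |
| 2 | 20.0% | 18.0% | 18/98 = 18.4% |
| 5 | 20.0% | 15.0% | 15/95 = 15.8% |
| 10 | 20.0% | 10.0% | 10/90 = 11.1% |

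Per never-cleared subject the shortfall is 1.0 point if left in ri. If censored it is (20.0 − 18.4)/2 ≈ 0.8 point at k = 2 and (20.0 − 11.1)/10 ≈ 0.9 point at k = 10.

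**Against the 0.9 threshold.** Upper 95% limits for Kaplan-Meier efficacy, treating the estimate as the proportion (80 + k)/100 when the subjects are left in ri, or 80/(100 − k) when they are censored:

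| k | Left in ri: efficacy | Wald | Exact | Wilson | Censored: efficacy | Wald | Exact | Wilson |
| --- | --- | --- | --- | --- | --- | --- | --- | --- |
| 0 | 80.0% | 87.8 | 87.3 | 86.7 | 80.0% | 87.8 | 87.3 | 86.7 |
| 2 | 82.0% | 89.5 | 89.0 | 88.3 | 81.6% | 89.3 | 88.7 | 88.0 |
| 3 | 83.0% | 90.4 | 89.8 | 89.1 | 82.5% | 90.04 | 89.5 | 88.8 |
| 4 | 84.0% | 91.2 | 90.6 | 89.9 | 83.3% | 90.8 | 90.2 | 89.5 |
| 5 | 85.0% | 92.0 | 91.4 | 90.7 | 84.2% | 91.5 | 90.9 | 90.2 |

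Under either handling the upper limit passes 90% at k = 3 (Wald), 4 (exact) or 5 (Wilson). At k = 2 or fewer no method crosses. The primary proportion stays at 80/100, with an upper limit of 86.7 to 87.8%, whatever k is.

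**A high-efficacy arm.** With 5 failures per 100, two of them never cleared, the failure rate is 5.0% if all are counted, 3/100 = 3.0% if the two are left in ri, and 3/98 = 3.1% if they are censored.

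**The case against.** The best defence is that the protocol never defines recrudescence, and its usage partly supports the sense of true failure as opposed to re-infection. The abstract uses PCR to separate failure from re-infection, the case report form's two substantive PCR results are reinfection and recrudescence, and B.3 calls the result a failure rate. On that reading a rescued non-clearer would be an event. This stands as far as intent goes, so one cannot say that such subjects will certainly be missed. It does not settle the wording. The protocol nowhere gives the term that meaning, and the case report form keeps ETF apart from the PCR result.

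A reader might go on to infer that the mefloquine-artesunate conclusion could be reversed. The documents do not support that. The 0.9 hypothesis concerns the proportion with ACPR, the primary analysis is the per-protocol proportion, and that proportion already counts every rescued non-clearer as a failure. No threshold is attached to the Kaplan-Meier estimate.

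It is also fair that the size rests on an assumed non-clearance rate, that the crossing point depends on an interval method the protocol does not name, and that the effect is zero if everyone clears.

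Nor are the extreme-case analyses a second defect. Assigning every lost subject as an event or a non-event gives the same count for those subjects under either name. Any error there is inherited from di.

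**Conclusion.** The point holds as a flaw in the event definition of a secondary estimator. Taken literally, B.3 leaves persistent parasitemia out of both di and the condition that defines ri, although B.1.e makes it part of treatment failure. Both ways of handling the affected subjects bias the Kaplan-Meier failure rate in the same direction, downward, by about 0.8 to 1.0 percentage point per never-cleared subject per 100.

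The consequence is a possible disagreement between the secondary and primary results, not a wrong primary result. In the 80% planning case that disagreement would straddle 0.9 once about 3 to 5 of the 20 failures were never-cleared. This assumes 100 evaluable subjects, complete follow-up and a non-clearance rate that the protocol does not supply.

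**What to change.** In B.3:

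- Define di as the number of subjects with treatment failure at ti. That means early or persistent failure (ETF, or a rescue prompt met without clearance), dated at the visit where it is met, plus PCR-confirmed recrudescence.
- Define ri as the number still under follow-up without treatment failure just before ti.
- State that PCR-confirmed re-infections are censored at detection.
- Reword the sensitivity-analysis sentence in terms of treatment failure so defined.
- State that this PCR-corrected estimate differs from the primary measure, which counts every subject needing alternative therapy, re-infections included.

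The change should not be presented as giving the two analyses the same event. B.1.e and the primary measure both include recurrences without PCR correction, so a difference remains and should be declared.

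The cost is a few sentences. The case report form already records ETF, the PCR result and the outcome date, so no new data are needed and no clinical rule changes. Kaplan-Meier efficacy may come out slightly lower.

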### 2. Objectives and Hypotheses

Primary Objective: To measure the proportion of uncomplicated *P. falciparum* malaria patients who have an adequate clinical and parasitological response following treatment with mefloquine- artesunate, piperaquine-DHA, or Malarone. It is important to note that the objective is to measure the efficacy of each individual regimen, rather than to compare the efficacies of each regimen, one to another.

Secondary Objective: To determine whether previously identified molecular markers of drug resistance, and in vitro drug resistance assays, predict clinical outcome for the three treatment regimens under study.

Primary Hypothesis: The upper bound of the 95% confidence interval for the proportion of ACPR in subjects treated with mefloquine-artesunate will be <0.9. The lower bound of the 95% confidence interval for the proportion of ACPR in subjects treated with piperaquine-DHA or Malarone will be >0.9.

Secondary Hypothesis: The odds ratio for treatment failure will be >2 in the following cases (a) patients treated with mefloquine artesunate whose Day 0 parasites have pfmdr1 copy number >1.5, (2) patients treated with Malarone whose Day 0 parasites have either *pfdhfr* S108N + N51I , or *pfcytb* Y268N. Mean IC50 values for treatment drugs will be statistically significantly higher in subjects who do not have ACPR than in those who do.

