#### f. Laboratory procedures

##### Malaria thick and thin blood films

Thick and thin blood smears will be stained with Giemsa and examined by a certified microscopist using 1000X oil immersion light microscopy. At least 200 ocular fields will be examined before a negative diagnosis is rendered. The microscopist records the number of asexual and sexual forms (separately) per 200 white blood cells in the thick smear. This is later converted to parasites/µl with a conversion multiple of 40 (assumes 8000WBC/µl) for analysis. All smears will be reviewed by a second certified microscopist at CNM. Slides for which results are discrepant will be reviewed by a third certified microscopist and the majority reading considered definitive. In the event that more than 10% of the reviewed slides show discrepancies, all study slides will be reviewed before data analysis.

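### The predictor analysis puts age and parasite density into categories before a p<0.05 screen for the logistic model, which lowers the chance that a graded risk factor is detected

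*Protocol*

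**What the plan says.** The paragraph on predictors of treatment failure in B.3 Data Analysis sets out three steps.

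- **Grouping.** "Subjects will be categorized based on therapeutic outcomes, presence of the various genetic markers and other demographic and parasite factors" The sentence continues with factors "that are putative determinants of treatment failure, e.g. age, parasite density, parasite clearance time".
- **Screening.** Associations with outcome are examined one variable at a time. The tests named are chi-square or Fisher's: "exact tests for two-tailed significance at p <0.05 will be used for univariate frequency comparisons".
- **Selection.** "Variables significant in any of these analyses will be fit into a logistic regression model"

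No cut-points are given for age or density, and no test for a numeric predictor is named in this paragraph. The same paragraph states the standing of the analysis: "Since this analysis is only powered to generate hypotheses, no correction will be made for multiple hypothesis testing".

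Both factors are numeric at source. The case report form (Appendix A) takes age in years and the asexual parasite count per 200 white cells, or per 1,000 red cells on dense slides. The laboratory section on blood films says "The microscopist records the number of asexual and sexual forms (separately) per 200 white blood cells in the thick smear" and "This is later converted to parasites/µl with a conversion multiple of 40".

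**The concern.** Eligible density runs from 1,000 to 100,000 parasites/µl, a 100-fold range, and age runs from 5 years with no upper limit. Cutting such variables into groups discards the differences within each group. Here that happens at the step that decides which variables are kept.

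The protocol has its own reason to care about age. B.1.a argues that partial immunity in adults can help clear even resistant parasites, so efficacy may look better in adults than in children. If age or density fails a weak screen, the model that estimates marker effects will not be adjusted for it.

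The protocol also waives multiplicity correction because the analysis is meant to generate hypotheses. That choice favours sensitivity, and categorising gives some of it away.

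**Working it through.** **Inputs from the protocol (B.2 Sample Size, B.3).** About 100 subjects per arm; 80% efficacy for mefloquine-artesunate, so 20% failures; 97.5% for each of the other two regimens; two-sided 0.05 at the screen. Pooled over arms, failures are (20 + 2.5 + 2.5)/300 = 25/300 = 8.3%.

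**The plan's own figure.** The predictor analysis has none. The nearest is 100 per group for 90% power at 95% v 80%. With pooled variance, n = [1.96·√(2 × 0.875 × 0.125) + 1.2816·√(0.0475 + 0.16)]² / 0.15² = (0.917 + 0.584)² / 0.0225, about 100.1, which rounds up to 101. It reproduces.

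**Assumptions not in the protocol.** The predictor x (age, or log density) is normal; logit(p) = a + b·x, with a set to give the stated failure rate; the cut is at the median.

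**Hand approximation.** For the continuous term, power ≈ Φ(b·√(n·p·(1−p)) − 1.96). A median split of a normal variable keeps a fraction 2/π = 0.637 of the information.

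- b = 0.45: 100 × 0.16 × 0.2025 = 3.24; Φ(1.80 − 1.96) = 44%. Split: 3.24 × 0.637 = 2.06; Φ(1.44 − 1.96) = 30%.
- b = 0.69: 100 × 0.16 × 0.476 = 7.62; Φ(2.76 − 1.96) = 79%. Split: 4.85; Φ(2.20 − 1.96) = 60%.

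**Simulation** (3,000 trials per setting; logistic likelihood-ratio test v median split). Chance of p<0.05:

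| n, failures | b (OR per SD) | OR, high v low half | Continuous | Chi-square | Fisher | Loss in points (chi-square / Fisher) |
|---|---|---|---|---|---|---|
| 100, 20% | 0.45 (1.57) | about 2.0 | 42.8% | 28.7% | 20.8% | 14.1 / 22.0 |
| 100, 20% | 0.60 (1.82) | about 2.6 | 63.4% | 44.2% | 34.2% | 19.2 / 29.2 |
| 100, 20% | 0.69 (1.99) | about 2.9 | 74.6% | 54.5% | 44.2% | 20.1 / 30.4 |
| 300, 8.3% | 0.45 (1.57) | about 2.05 | 57.8% | 38.1% | 31.1% | 19.7 / 26.7 |

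With no true effect, the continuous test rejects in 5.7–5.9% of trials and chi-square in 5.9–6.1%, so the gain does not come from extra false positives.

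**Second simulation** (1,500 trials per setting; score test for the continuous term):

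| n, failures | OR per SD | Continuous | Chi-square | Fisher |
|---|---|---|---|---|
| 100, 20% | 2.0 | 74% | 54% | 43% |
| 100, 20% | 1.5 | 33% | 24% | 16% |
| 100, 5% | 2.0 | 31% | 18% | 5% |
| 300, 10% (assumed) | 2.0 | 94% | 78% | 72% |
| 300, 10% (assumed) | 1.5 | 55% | 35% | 31% |

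Tertiles by chi-square do no better than the median split: 52% at n = 100 with 20% failures and 78% at n = 300, both at OR 2.0.

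**A threshold instead of a gradient.** Let the lowest quarter of x differ from the rest by OR 3, with n = 100 and 20% failures. A cut exactly at the threshold gives 56% (chi-square) or 51% (Fisher), against 37% for the continuous term. Under the same step effect a median split gives only 25% or 17%.

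**The case against.** The best defence is that the wording is looser than it looks. Chi-square and Fisher are tied to frequency comparisons, and no sentence forbids another test for numeric factors. The paragraph is also not a full list of tests, because A.2 Objectives and Hypotheses plans a comparison of means: "Mean IC50 values for treatment drugs will be statistically significantly higher in subjects who do not have ACPR than in those who do". That is fair, so a reader should not infer that the protocol bars a continuous analysis. What stands is that age and density appear as examples of factors used to categorise subjects, and that the paragraph names no other test for them.

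Cut-points may be set in a statistical analysis plan that is not shown, so their absence here is no fault, and nothing proposes choosing them from the data. Setting cut-points would still not recover the loss, which comes from categorising.

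The shape of the effect matters. B.1.a contrasts adults with children, which would fit a threshold, and a cut placed exactly there beats a linear term. But the protocol gives no threshold, and a cut in the wrong place loses again.

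Few failures also limit detection. At 5% failures in one arm, even the continuous test passes only 31% of the time at OR 2.0 per standard deviation.

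Finally, unadjusted marker effects come from the p<0.05 gate, not from categorising as such. Making the variables continuous does not cure that unless they also enter regardless of the screen.

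**Conclusion.** The point holds as a loss of sensitivity. At the protocol's planning figures for one arm (100 subjects, 20% failures), a median split lowers the chance that a true graded predictor passes the screen by about 14 to 20 points with chi-square and 22 to 30 with Fisher, for odds ratios of about 1.6 to 2.0 per standard deviation. At 1.5 the loss is smaller, about 9 and 17 points (33% − 24% and 33% − 16%). These sizes rest on a normal predictor, a linear logit effect and a median cut, none of which the protocol states; nor does it say whether arms are pooled.

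A reader might infer that real risk factors are bound to be missed and never reach the model. The figures do not show that: the categorised screen still passes 29–55% of the time with chi-square in the first simulation at n = 100, and 72–78% at n = 300 for OR 2.0 in the second.

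The primary efficacy estimates are untouched, and the analysis is declared hypothesis-generating. This is an improvement worth making, not a flaw in the trial's main conclusion.

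**What to change.** In B.3, under predictors of treatment failure:

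1. Test age and log10 Day 0 parasite density as continuous terms in univariable logistic regression (likelihood-ratio test; odds ratio per standard deviation or per 10-fold density). Add a quadratic term to check linearity.
2. Enter both in that form in the multivariable model, ideally whatever their univariable p-value, so that marker effects are adjusted for them.
3. Keep chi-square or Fisher for truly categorical factors such as SNPs and sex, and keep the pre-specified pfmdr1 copy number >1.5 contrast from A.2. Grouped tables can still be shown descriptively.

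The cost is a change of wording, with no new data. The small downside is the linearity assumption: if a true threshold were known, a cut placed there would do better. With about 20 failures in the mefloquine-artesunate arm and fewer expected in the others, entering the two terms regardless also uses up part of a small model.

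### Parasite clearance time is tested as a predictor of treatment failure although never clearing is itself failure, so part of any association is built in (minor; exploratory analysis only)

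*Protocol*

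**What the plan says.** The outcome is fixed in three places in the protocol.

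- Section B.1.e, under rescue therapy, defines the event: "Treatment failures, defined as persistent or recurrent parasitemia during the 42-day follow-up".
- Section B.1.g (Follow-up) lists three triggers for rescue: "Asexual parasitemia on day 2 > day 0", "Asexual parasitemia fails to clear by day 4" and "Asexual parasitemia recurs on or between days 4 and 42".
- Section B.3 (Data Analysis) measures efficacy as "the percent of subjects not requiring alternative therapy during the 42-day course of the test", so rescue for any of the three reasons counts against the regimen.

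The predictor analysis, also in B.3, gives as examples of the candidate determinants of failure "age, parasite density, parasite clearance time". The test is specified: "Chi square or Fisher’s exact tests for two-tailed significance at p <0.05 will be used for univariate frequency comparisons". Factors that reach significance go into one logistic regression. No multiplicity correction is made, because the analysis is meant only to generate hypotheses.

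**The concern.** Clearance time and failure share a component. A subject still parasitemic past day 4 has a long (or never observed) clearance time and is, for that same reason, a failure. The two variables are then associated whether or not clearance speed says anything about later recrudescence. PCR correction does not help, because persistent parasitemia is not re-infection.

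At stake is how a positive result would be read. A significant odds ratio would suggest that slow early response foretells late recrudescence, when it might only restate the failure definition. A hypothesis drawn from an overlap of definitions is not worth following up. If clearance time is cut at day 4, the slow group contains only failures: the odds ratio is infinite and the logistic model separates.

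**Working it through.** The protocol gives no figure for this point, so there is nothing to reproduce. The structure follows from the sections cited above; the arithmetic only shows how large the effect could be.

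**Inputs from the protocol.** About 100 subjects per arm and, for mefloquine-artesunate, 80% expected efficacy (B.2), hence 20 failures and 80 non-failures. Fisher's exact test, two-sided, 0.05 (B.3).

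**Assumptions not in the protocol.** Day-3 smear positivity stands in for slow clearance; day 3 is the last scheduled visit before day 4. A fraction b of all other subjects is positive on day 3, equally among late failures and non-failures, so there is no true link. Of the 20 failures, k are early failures and are positive on day 3.

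**Expected odds ratio.** Among failures, positives number k + b(20 − k) and negatives (1 − b)(20 − k). Among non-failures, positives number 80b and negatives 80(1 − b). Therefore

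OR = {[k + b(20 − k)] / [(1 − b)(20 − k)]} × {(1 − b)/b} = 1 + [k/(20 − k)]/b.

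**Rejection rate.** Draw X from Binomial(20 − k, b) and Y from Binomial(80, b). Form the table with rows (k + X, 20 − k − X) and (Y, 80 − Y), and add up the probability of all tables with Fisher p<0.05.

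With b = 0.10:

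| Early failures k | OR | Fisher p<0.05 |
| --- | --- | --- |
| 0 | 1.0 | 3% |
| 1 | 1 + (1/19)/0.10 = 1.5 | 6% |
| 2 | 1 + (2/18)/0.10 = 2.1 | 14% |
| 4 | 1 + (4/16)/0.10 = 3.5 | 47% |
| 6 | 1 + (6/14)/0.10 = 5.3 | 87% |

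With b = 0.05, one early failure gives 1 + (1/19)/0.05 = 2.1 and 7%; four give 1 + (4/16)/0.05 = 6.0 and 79%.

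**A second set-up.** Let a share e of all subjects fail by non-clearance. Among those who clear, let a share s be slow, and let 10% recur regardless of speed. Then OR = 1 + e/[(1 − e) × s × 0.10]. With e = 2% and s = 10%, OR = 1 + 0.02/(0.98 × 0.10 × 0.10) = 3.0. For s from 5% to 20%, the odds ratio runs from 5.1 down to 2.0. Simulated Fisher rejection runs from 38% down to 17% with 100 subjects, and from 82% down to 40% if all 300 are pooled. With e = 0 the odds ratio is 1.0 and rejection is 2–4%.

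**Check of the repair.** If the k early failures are left out of the first set-up and only subjects who cleared are compared, the expected odds ratio returns to 1.0. Fisher rejection is then about 2% for each k from 1 to 6 in the table.

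**The case against.** Four points can be made for the plan.

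1. **The size is unknown.** No early-failure rate is stated. With none the built-in part disappears, and with one per arm the error rate is close to nominal. This stands: a reader might infer that a spurious predictor is bound to appear, and the protocol does not support that.

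2. **Coding is open.** B.3 fixes neither a cut-off nor a value for subjects who never clear. If they were coded as missing they would drop out, and the overlap with them. A subject rescued because the count rose by day 2 has clearance cut short by rescue and need not be positive on day 3. Coding of this kind can reasonably be left to an analysis plan. This narrows the point, but B.3 does name the variable, the outcome, the test and the rule for entering the model, and none of these confines the analysis to subjects who cleared. The case report form records early and late failure separately, so the data would allow that restriction; B.3 does not call for it.

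3. **Early response is a legitimate predictor.** Among subjects who clear, clearance time may truly predict recurrence, and measurement after treatment is no fault in a predictive model. This is accepted, and the fix keeps that analysis.

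4. **The secondary hypothesis is not reached.** A reader might infer that clearance time in the joint model distorts the marker odds ratios on which that hypothesis rests. Section A.2 states those odds ratios by Day 0 marker status with no adjustment, and B.3 tests markers one at a time. The logistic model is a later step, and B.3 does not make it the estimator for A.2. The inference is not supported.

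The exploratory label lowers the weight of the point. It explains the lack of multiplicity correction, but it does not remove an overlap between predictor and outcome.

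**Conclusion.** The point holds in a limited form, and its severity is minor. Under the protocol's own definitions, the association between clearance time and failure is built in for subjects who never clear. For subjects who clear and later recur, it is not.

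The artefact runs from nothing, with no early failures, to an odds ratio of about 5 that would usually be declared significant, with six early failures among 20. That range rests on the assumed background positivity, on day-3 positivity as a proxy for slow clearance, and on an early-failure count that the protocol does not supply. The exploratory predictor analysis is affected. The primary efficacy estimate and the unadjusted, one-at-a-time marker comparisons are not.

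**What to change.** In the predictor paragraph of B.3, state that clearance time will be analysed only among subjects who cleared, against later recurrence (PCR-confirmed recrudescence), counted from a landmark after clearance that is fixed in advance, such as the day 7 visit. State that early failures will be tabulated separately by regimen. If the multivariable model is also used to report odds ratios for baseline markers, present it without clearance time, because that variable is measured after treatment and could absorb part of a marker's effect.

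This takes two or three sentences and no new data, since smears and failure type are already on the case report form. The cost is that early failures, and any recurrence before the landmark, do not contribute to the clearance-time analysis. No treatment or rescue rule is touched.
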